##### MMG (Experimental Condition)

This is a 12-week group that meets for 90 minutes weekly. This group will draw on interventions developed in our pilot study (described above). The protocol will be further revised based on IM steps followed for aims 1 and 2.

##### PCGT (Control Condition)

This is a time-limited treatment for PTSD that focuses on increasing adaptive responses to current life stressors and difficulties that are directly or indirectly related to trauma or PTSD symptoms. PCGT was initially developed as a nonspecific comparison condition to test the effectiveness of trauma-focused cognitive behavioral therapy [57]. To justly compare it to MMG, PCGT will be delivered for a 12-week period. The basis of PCGT is to provide “common factors” of psychotherapy and help articulate whether the effect of MMG is due to bringing men together in a group setting or delivering treatment that is specifically oriented to men (such as MMG).

### Data and Outcome Measures

The following primary and secondary outcomes will be measured at baseline, treatment completion, and 6-month follow-up.

#### Primary Exploratory Outcomes

The Recovery Assessment Scale (RAS) is a 41-question forced-choice 5-level Likert rating scale designed to assess recovery, with emphasis on agency, hope, belongingness, and shame reduction—key constructs postulated to impact and be expressive of psychological distress and intra- and interpersonal avoidance [58]. The External and Internal Shame Scale (EISS) assesses global shame experiences, with attention to its external and internal dimensions relevant to men’s MST (Figure 1) [59]. The scale consists of 8 items and measures 4 central shame domains: inferiority and inadequacy, sense of exclusion, uselessness and emptiness, and criticism and judgment. The General Belongingness Scale (GBS), a 12-item measure rated on a 7-point Likert scale, assesses a general sense of belonging, another indication of interpersonal distress pertaining to MST [60].

#### Secondary Exploratory Outcomes

The PTSD Checklist for DSM-5 (PCL-5) is a 20-item non–MST-specific self-report measure that assesses the *Diagnostic and Statistical Manual of Mental Disorders*, 5th edition, symptoms of PTSD, a common indicator of MST-related distress [61]. Each symptom is rated on a 5-point Likert scale assessing distress. The Patient Health Questionnaire–9 (PHQ-9) is a widely used brief, 9-item instrument for screening, monitoring, and measuring the severity of depression over the course of 2 weeks. The PHQ-9 is a reliable and valid measure of depression severity that assesses symptoms, including suicidality, that are consistent with the *Diagnostic and Statistical Manual of Mental Disorders*, 5th edition, criteria for depression [62].

### Analysis

Following the CONSORT (Consolidated Standards of Reporting Trials) extension for randomized pilot and feasibility trials [63], the limited dataset will be underpowered to detect differences between conditions, and we did not design this pilot RCT to have power to examine or establish efficacy; rather, we are seeking to pilot the refined intervention to assess engagement outcomes, change in theorized targets, and initial clinical signals. Any missing data will be identified during analysis and noted in write-ups. We will use a linear mixed model for longitudinal data with a 2-level factor for group and a 3-level factor for time. The experimental and control groups will form the 2-level between-group factor, and the 3 time points (baseline, after treatment, and 6-month follow-up) will form the within-group factor.

To pretest the intervention, we will test the experimental vs control groups on exploratory data on clinically meaningful outcomes from baseline to after treatment. We hypothesize that participants assigned to the MMG will report improved engagement (session attendance) and comparable signs of recovery (agency, hope, belongingness, and shame reduction) and PTSD, depression, and suicidality measurements. This hypothesis will compare the impact of the MMG to that of PCGT at the posttreatment time point and 6-month follow-up (both as compared to baseline). Both comparisons will include psychometrically validated measures (RAS, EISS, GBS, PCL-5, and PHQ-9) and attendance.

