### Aim 2: Pilot Trial

#### Overview

Using the revised protocol, we will conduct a pilot RCT of the MMG vs present-centered group therapy (PCGT; control condition) at an outpatient VAGLA mental health clinic (IM step 6). Over 24 months, male survivors of MST (n=32) will be randomized to the MMG or PCGT group (4 cohorts: 2 experimental and 2 control). We will investigate engagement (session attendance) as well as recovery-oriented outcomes (agency, hope, belongingness, and shame reduction) and psychological symptoms (PTSD, major depressive disorder, and suicidality) assessed before, immediately after, and 6 months after the intervention.

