#### Participant Recruitment and Randomization

We will begin recruiting male survivors of MST through collaboration with VAGLA outpatient mental health clinics (ie, primary care, mental health clinics, trauma recovery services, substance use disorder clinics, and domiciliary services). During standard clinical care, health care professionals will inform male survivors of MST about the opportunity to participate in a study on men’s MST. These veterans will receive an informational study handout, which will also be publicly available. This handout will state that veterans will potentially receive financial compensation for baseline data collection. Interested veterans will be screened for eligibility and contact the study coordinator to provide written consent and arrange the collection of pretreatment data.

Individuals who do not meet the exclusion criteria (see below) will be randomly assigned to 1 of the 2 study groups: the MMG (n=8) or PCGT control (n=8). The process will be repeated for the second cohort. Participant randomization will be performed using a computer-generated randomization sequence prepared by an independent statistician, with allocation concealment maintained until assignment. Due to the nature of the intervention, participants cannot be blinded following treatment assignment. Because primary outcomes are patient reported, blinded outcome assessment is not feasible.

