#### Design

##### Overview

This pilot RCT will involve 12 weekly in-person sessions with an interventionist at the West Los Angeles Mental Health Clinic. The principal investigator (PI) will serve as the primary interventionist for the experimental condition during the first cycle, and a different staff psychologist will serve as the interventionist for the experimental condition during the second cycle. To distribute and minimize potential health care professional burden, 2 additional staff psychologists from Trauma Recovery Services Clinic (1 per cycle) will serve as interventionists for the control condition. All group sessions will be audio recorded for fidelity. Participant retention will be enhanced through financial compensation for trial participation. Participants will receive US $100 for completion of a pretreatment survey, US $50 for completion of the posttreatment survey, and US $50 for completion of the 6-month survey and interview.

While having the PI conduct the first experimental condition risks bias, this was strategically designed for three key reasons: (1) the PI developed the MMG treatment protocol and, thus, is most familiar with the approach; (2) it will allow for any needed protocol adjustments in preparation for training of another clinician for the second cohort; and (3) this will be a pilot RCT designed to assess appropriateness and feasibility for a future trial.

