## Discussion

Men with histories of MST are an important yet underserved veteran population. Shame and disruptions related to masculine identity may contribute to substantial distress and treatment underuse, highlighting the need for research that addresses the specific clinical needs of this population. Existing treatments are valuable but were not developed specifically to address men’s MST-related identity concerns. This study addresses that gap by refining and piloting the MMG, a group psychotherapy intervention designed specifically for men with histories of MST and that has demonstrated previous preliminary clinical benefit. We anticipate that this pilot will provide preliminary evidence regarding the feasibility, acceptability, and potential clinical utility of this gender-tailored group intervention.

The protocol has several methodological strengths. First, the iterative intervention refinement approach guided by the IM and ARM frameworks incorporates perspectives from veterans, clinicians, and an MST expert panel. Second, this protocol is designed to examine key implementation factors and for future implementation considerations by exploring engagement, dropout, barriers, and facilitators. Third, the mixed methods integration provides a richer understanding of feasibility and preliminary clinical effects, where quantitative outcomes can characterize clinical benefit and qualitative data can explore context and acceptability, which will be useful for future research on men with histories of MST.

Several limitations should be considered when interpreting findings from this pilot study. First, the pilot sample size, designed for feasibility and clinical signal to inform future research, is underpowered for efficacy testing. Second, this protocol will be conducted at a single site, and implementation may vary across VA facilities. Third, there is potential for selection bias given that men willing to participate in a group therapy trial for MST may differ from a more representative sample of men with MST, who may be less likely to seek MST-focused care and participate in group interventions. Fourth, therapist effects may influence outcomes, particularly given that the intervention was initially delivered and will be tested by the PI; fidelity monitoring and standard intervention procedures will help mitigate this concern.

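### The planned mixed model names only arm and time, although the 32 men are treated in four therapist-led groups; standard errors for MMG vs PCGT are too small if outcomes correlate within group

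*Protocol article*

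**What the plan says.** **Randomization and delivery.** The Aim 2 Overview says that "male survivors of MST (n=32) will be randomized to the MMG or PCGT group", and counts "4 cohorts: 2 experimental and 2 control". Participant Recruitment and Randomization gives 8 men to MMG and 8 to PCGT, then adds: "The process will be repeated for the second cohort". Men are thus randomized individually and treated in groups of 8.

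**Therapists.** Under Design, Overview, the principal investigator "will serve as the primary interventionist for the experimental condition during the first cycle", and a different staff psychologist leads the second MMG group. For PCGT, "2 additional staff psychologists from Trauma Recovery Services Clinic (1 per cycle) will serve as interventionists for the control condition". That makes four therapists for four groups, one each. The same section says that having the principal investigator lead the first MMG group leaves room to adjust the protocol before the second.

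**Model.** The Analysis section after the outcome measures says: "We will use a linear mixed model for longitudinal data with a 2-level factor for group and a 3-level factor for time". It then defines the between-group factor as experimental against control. Therapy group, therapist and cycle are not mentioned. Arms are to be tested and compared after treatment and at 6 months, each against baseline, on RAS, EISS, GBS, PCL-5, PHQ-9 and attendance. MMG is expected to do better on engagement and to be comparable on recovery and symptoms. Power for efficacy is disclaimed.

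**Therapist effects.** The Discussion lists them as a limitation and answers that "fidelity monitoring and standard intervention procedures will help mitigate this concern".

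**The concern.** Men in one therapy group share a therapist, peers and twelve weeks of discussion, so their outcomes and attendance may be alike for reasons unrelated to arm. The article's own rationale makes this likely: the Introduction presents belonging, mutual recognition and social support as reasons why a group should work, and belongingness and shame are among the primary exploratory outcomes. A possible protocol adjustment between the two MMG groups is a further reason why they may differ.

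A model with arm and time, even with within-person correlation, treats the 32 men as independent. The arm contrast actually rests on two groups against two. Ignoring this affects both halves of the hypothesis. A difference in attendance may reflect one therapist or one cohesive group. If comparability is judged by how tightly an interval sits around zero, an interval that is too narrow makes it look better established than it is.

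**Working it through.** **Inputs from the article.** Therapy groups: 4, two per arm (Aim 2 Overview). Size: m = 8 (Participant Recruitment and Randomization). Therapists: one per group (Design, Overview).

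**Assumptions.** The article gives no ICC and no significance level. I take ICC from 0 to 0.15 and two-sided 5%, with total variance set to 1.

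**The plan's own figure.** 2 cycles × (8 + 8) = 32, which agrees with the stated sample size.

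**Standard error at one time point.**

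1. Design effect: DE = 1 + (m − 1) × ICC = 1 + 7 × ICC.
2. The variance that the naive analysis estimates also shrinks, because members of one group resemble each other. With n = 16 per arm, E[s²] = (1 − ICC) + ICC × (16 − 8)/(16 − 1) = (1 − ICC) + ICC × 8/15.
3. True SE divided by naive SE = √(DE / E[s²]). The square root of DE alone would understate this ratio.
4. Effective sample size = 32 / DE.
5. Type I error: 100,000 simulated trials with two groups of 8 per arm and a t-test on 30 df that ignores therapy group.

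| ICC | DE | E[s²] | True SE / naive SE | Effective N | Type I error, naive |
|---|---|---|---|---|---|
| 0 | 1.00 | 1.000 | 1.00 | 32.0 | 5.1% |
| 0.05 | 1.35 | 0.977 | 1.18 | 23.7 | 9.3% |
| 0.10 | 1.70 | 0.953 | 1.34 | 18.8 | 13.8% |
| 0.15 | 2.05 | 0.930 | 1.48 | 15.6 | 18.0% |

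A test on the four group means (2 df) kept its error rate at about 5.0% throughout.

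**Fewer men per group.** The article expects about 7 dropouts. If these men also lost their outcome data, evenly across groups, then m = (32 − 7)/4 = 6.25, and the ratios become 1.14, 1.26 and 1.39.

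**Does the longitudinal model behave alike?** Take a random-intercept model with arm × time, person variance 0.5, residual variance 0.5 at baseline, and a group effect of variance ICC only after baseline, replacing part of the residual. The true variance of the arm difference in change is (1 − ICC)/8 + ICC. At ICC 0, 0.05 and 0.10 this is 0.125, 0.169 and 0.213, so the SE is 0.354, 0.411 and 0.461. The mean model SE in 400 simulated trials was 0.350, 0.345 and 0.331. The ratios are 1.01, 1.19 and 1.39, close to the table. The observed spread in those 400 runs gave 1.06, 1.13 and 1.41; the 1.06 at ICC 0 shows how noisy so few runs are.

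**What an interval would look like.** The half-width of a 95% interval, in SD units, is t × √(2/16 × DE), with t = 2.04 on 30 df and 4.30 on 2 df:

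| ICC | 30 df | 2 df |
|---|---|---|
| 0 | 0.72 | 1.52 |
| 0.05 | 0.84 | 1.77 |
| 0.10 | 0.94 | 1.98 |
| 0.15 | 1.03 | 2.18 |

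At ICC 0.05 to 0.15, the naive interval would have a half-width of about 0.71 SD or slightly less. The choice of degrees of freedom matters more here than the choice of ICC.

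**The case against.** **The SAP may deal with it.** The article gives the factor layout and no random effects, covariance structure or degrees-of-freedom method, which an article commonly leaves to the SAP. A therapy-group term could be there. This stands in part: one may say that the article names no such term, not that it excludes one. But the article does fix the factors and defines group as arm. Where it turns to therapist effects, it offers only fidelity monitoring and standard procedures, and nothing in the analysis.

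**It is a pilot.** Outcomes are labelled exploratory, efficacy is disclaimed, and low power and therapist effects are listed as limitations. This lowers the severity. It does not remove the point, since the article still says that the arms will be tested, and low power does not excuse an understated standard error.

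**The Discussion makes no claim about variance.** That is fair. Its sentence is about influence on outcomes, chiefly from the principal investigator's role, and claims only partial mitigation. It is incomplete rather than false.

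**Three stronger readings that the article does not support.** A reader might infer that every interval will be too narrow; that needs an ICC above 0, and none is given. A reader might infer that therapist cannot be told apart from arm at all. With two therapists per arm, therapist is nested in arm, so variation between therapists can in principle be estimated, on 2 df; what cannot be separated is therapist from therapy group. A reader might also infer that a false signal would trigger the multisite trial. The end of the Discussion ties that trial to feasibility and a viable implementation pathway, not to an arm p-value.

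**Conclusion.** The point holds, at moderate severity. As written, the model leaves out the therapy group, and the standard errors for MMG vs PCGT would be too small at any positive ICC. The understatement is about 1.18-fold to 1.48-fold for ICCs of 0.05 to 0.15 with 8 men per group, and somewhat less with smaller groups. These sizes rest on assumed ICCs, equal groups and a single-time-point approximation, which the longitudinal check supports in direction and rough size. What is at stake is false precision in the exploratory signal, including in any statement that the arms are comparable.

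**What to change.** **Analysis section.**

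- Name therapy group as a source of variance, and say that it is nested in arm and inseparable from therapist.
- Four groups cannot estimate that variance reliably, so a random term alone is not enough. Report arm differences as estimates with 95% confidence intervals at prespecified ICCs, for example 0, 0.05, 0.10 and 0.15.
- State the degrees of freedom used. A group-level analysis has 2 df (critical t = 4.30), or 1 df if cycle is also fitted (four group means less intercept, arm and cycle).
- Show results for each of the four therapy groups.
- Treat any p-value for an arm difference as descriptive. P-values need not be banned.

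**Discussion.** Add to the therapist-effects limitation that fidelity monitoring does not remove correlation within a therapy group, and that each arm's result rests on two therapist-led groups.

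**Cost.** Analysis wording and wider intervals; no new participants or data. The article says that recruitment for the pilot trial has not begun, so this can still be prespecified.

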#### Data Collection

Veterans who are screened as eligible but decline to enroll (n≈7) will be invited to participate in a brief (5-20 minute) interview to understand their reasons for declining and their history (if any) of use of and experiences with MST-related services and mental health services more broadly to align with the ARM. In addition, those who enroll but drop out before treatment completion (n≈7) and all completers (n≈16) will be invited for 20- to 45-minute interviews. All interviews will be arranged within a reasonable period. We estimate interviewing a total of 30 veterans, with the assumption that approximately half of RCT completers will not participate in interviews due to attrition, lack of interest, and other unforeseen barriers. We will intentionally recruit a diverse sample of participants in terms of racial and ethnic identities, ages, and sexual orientations to explore intersectionality. All veterans who participate in interviews will receive financial compensation.

Semistructured interviews with interventionists will solicit information regarding (1) clinician perceptions of men’s engagement; (2) quality and effectiveness of the intervention; and (3) quantitative data on acceptability, appropriateness, and feasibility of the interventions based on brief 4-item measures (Acceptability of Intervention Measure, Intervention Appropriateness Measure, and Feasibility of Intervention Measure) [64].

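### Reading the arm effect as change from baseline is valid, but less precise than conditioning on the baseline scores already collected

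*Protocol article*

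**What the plan says.** The Analysis section for the Aim 2 pilot trial (protocol article) gives the model in two sentences: "We will use a linear mixed model for longitudinal data with a 2-level factor for group and a 3-level factor for time", and "the 3 time points (baseline, after treatment, and 6-month follow-up) will form the within-group factor". It then places the MMG versus PCGT comparison "at the posttreatment time point and 6-month follow-up (both as compared to baseline". No baseline covariate is mentioned, nor any constraint that the arms share a baseline mean.

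Baseline values exist for every scale (RAS, EISS, GBS, PCL-5, PHQ-9). Data and Outcome Measures says: "The following primary and secondary outcomes will be measured at baseline, treatment completion, and 6-month follow-up". On timing, Participant Recruitment and Randomization has interested veterans "contact the study coordinator to provide written consent and arrange the collection of pretreatment data", and describes random assignment after that.

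**The concern.** Randomization makes the two arms' true baseline means equal, provided baseline is recorded before allocation is known. A model that still estimates a separate arm difference at baseline, and subtracts it, carries the sampling error of that difference into each follow-up contrast. Conditioning on baseline removes only the part of the imbalance that predicts follow-up, so it is at least as precise in large samples for any correlation below 1.

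Precision is scarce here. With 16 men per arm, chance baseline imbalance is not small. The section says that the trial is meant to look for initial clinical signals, and it expects recovery and symptom scores to be comparable between arms. What can be said about either depends on how wide the intervals are.

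**Working it through.** **Inputs**

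- Sample size: "male survivors of MST (n=32) will be randomized to the MMG or PCGT group (4 cohorts: 2 experimental and 2 control" (Aim 2 Overview). Each cycle allocates "the MMG (n=8) or PCGT control (n=8" participants and is run twice, so 2 × (8 + 8) = 32, or n = 16 per arm. The two places agree.
- The article states no power, alpha, SD or effect size for the between-arm contrast, so there is no power figure to reproduce.
- rho, the baseline-to-follow-up correlation, is not given. It is assumed, and a range is shown.
- Missing follow-up: Aim 3 Data Collection expects "those who enroll but drop out before treatment completion (n≈7" participants, and 7/32 = 22%. This counts treatment dropout. Using it as a rate of missing follow-up is an assumption.

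**Formulas** (SD units, equal SDs, independent men, 2/n = 2/16 = 0.125)

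- Change from baseline: variance = 2(1 − rho) × 0.125
- Conditioning on baseline: variance = (1 − rho²) × 0.125
- Ratio, conditioned to change = (1 + rho)/2

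| Assumed rho | Variance, change | Variance, conditioned | Ratio | SE, change | SE, conditioned | Total N for change scores to match 32 |
|---|---|---|---|---|---|---|
| 0.3 | 0.175 | 0.114 | 0.65 | 0.418 | 0.337 | 49 |
| 0.5 | 0.125 | 0.094 | 0.75 | 0.354 | 0.306 | 43 |
| 0.7 | 0.075 | 0.064 | 0.85 | 0.274 | 0.252 | 38 |
| 0.9 | 0.025 | 0.024 | 0.95 | 0.158 | 0.154 | 34 |

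The last column is 32 divided by the ratio. At rho = 0.5 the 95% half-width (normal approximation) falls from 1.96 × 0.354 = 0.69 SD to 1.96 × 0.306 = 0.60 SD. A comparison of follow-up scores that ignores baseline has SE √0.125 = 0.354 at any rho. Below rho = 0.5 the change contrast is therefore worse than making no use of baseline.

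**Check on the full three-time-point model.** Generalized least squares with the arms free at baseline gives exactly the change-score SE when data are complete (0.354 at rho = 0.5; 0.274 at 0.7). Constraining baseline gives 0.306 and 0.252.

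**Less favourable conditions**

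| Condition | Ratio at rho 0.5 | Ratio at rho 0.7 | Ratio at rho 0.9 |
|---|---|---|---|
| Complete data, formula | 0.75 | 0.85 | 0.95 |
| 22% missing both follow-ups | 0.79 | 0.88 | not run |
| 20,000 simulated trials, N = 32, slope estimated | 0.77 | 0.88 | 0.99 |

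The approximate small-sample factor for estimating the slope is 1 + 1/(32 − 4). Setting (1 + rho)/2 × 29/28 = 1 gives break-even near rho = 0.93.

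**Clustering.** Treatment is given in four groups. Group-level variance that arises after baseline adds to both estimators alike. If it adds an assumed 0.05 SD² to the contrast variance, the ratio at rho = 0.5 becomes (0.094 + 0.05)/(0.125 + 0.05) = 0.82.

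**Chance imbalance.** The SE of the baseline arm difference is 0.354 SD, so the chance of a difference above 0.5 SD on a given scale is 2 × [1 − Φ(0.5/0.354)] = 0.16.

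**The case against.** The strongest reply is that the article never says the arms are free at baseline. A common-baseline model also has two groups, three time levels and contrasts at both follow-ups, and an article may leave such detail to the full plan. It is true that the free-baseline model is an inference. But it is the ordinary reading of a group factor, a time factor that includes baseline and effects expressed relative to baseline. The point therefore concerns a stated analysis that can be made more precise, not only a missing detail.

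It is also fair that this is efficiency and not error. The pilot is declared underpowered, no efficacy decision depends on the contrast, and the interval at rho = 0.5 is wide either way. The one directional hypothesis concerns attendance, which has no baseline value and is untouched. These arguments limit the weight of the point but do not justify choosing the noisier estimator.

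A further condition stands. The constraint needs baseline to be completed before allocation is known. The recruitment text has its collection arranged before assignment is described, but does not say that it is finished by then, and the outcomes are unblinded self-report.

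A reader might also infer that, because no group-by-time term is written out, the model has main effects only, so that averaging in the pre-treatment visit shrinks the effect by a third. The document does not support this. The same section asks for arm comparisons at two specific times relative to baseline, which a main-effects model cannot produce.

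**Conclusion.** The point holds as a matter of precision. As ordinarily fitted, the planned contrast is a difference in change scores: unbiased under randomization, but less precise than conditioning on baseline. Under assumed rho of 0.5 to 0.7 the variance given up is about 25% to 15% with complete data. It is about 21–23% at 0.5 and 12% at 0.7 after allowing for either 22% missing follow-up or the cost of estimating the slope. It is negligible near 0.9, and the relative gain is smaller still with clustering in the therapy groups. No single percentage can be stated as fact, because rho, the missing-data rate and the clustering are all unknown. The consequence is wider intervals on the scale outcomes, not bias or a missed power target.

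**What to change.** For RAS, EISS, GBS, PCL-5 and PHQ-9, adopt one of the following:

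- Keep the mixed model with all three time points, but give the arms a common baseline mean: fixed effects for time, arm-by-post-treatment and arm-by-6-month, no arm term at baseline, and unstructured within-person covariance.
- Use the two follow-ups as outcomes, with the baseline score as a covariate.

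Report the arm difference at post-treatment and at 6 months, with its interval, from that model. Leave attendance out of this change. State that baseline surveys are completed before allocation is revealed, or confirm it in the procedures.

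The cost is a sentence or two in the analysis plan. No new data, visits or software are needed. The article reports that Aim 2 recruitment has not begun and that the trial is planned for January 2027, so the change can be fixed before any outcome is seen.

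### The pilot hypothesises comparable recovery and symptoms, but its between-group comparison of 32 men has no criterion for comparability, so a non-significant result could be misread as support

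*Protocol article*

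**What the plan says.** All of this stands in the aim 2 Analysis section of the protocol article, which follows the outcome measures.

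- **Hypothesis.** "We hypothesize that participants assigned to the MMG will report improved engagement (session attendance) and comparable signs of recovery". The sentence goes on to include PTSD, depression and suicidality. Superiority is expected for attendance only.
- **Outcomes covered.** "Both comparisons will include psychometrically validated measures (RAS, EISS, GBS, PCL-5, and PHQ-9) and attendance". These five scales are all three primary exploratory outcomes (RAS, EISS, GBS) and both secondary ones (PCL-5, PHQ-9). The contrasts are at posttreatment and 6 months, each against baseline.
- **Analysis.** "To pretest the intervention, we will test the experimental vs control groups on exploratory data on clinically meaningful outcomes from baseline to after treatment". The model is given as follows: "We will use a linear mixed model for longitudinal data with a 2-level factor for group and a 3-level factor for time".
- **Precision.** "the limited dataset will be underpowered to detect differences between conditions". The section adds that the pilot was not designed to establish efficacy and looks for initial clinical signals.

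The article names no equivalence or non-inferiority test, margin, interval criterion or other definition of comparable. It also states no alpha and no rule for interpreting a non-significant result.

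**The concern.** The hypothesis and the analysis point in opposite directions. A test of MMG against PCGT looks for a difference, while the hypothesis for the clinical scales is that no important difference exists. Without a criterion for comparability, the only way the stated test could appear to support the hypothesis is by failing to find a difference. In a trial that declares itself underpowered for differences, that outcome is likely across a wide range of true effects, including some that would matter to patients. Low power usually works against a hypothesis, but here it works in its favour.

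At stake is what the pilot is taken to have shown. Its results go to the expert panel under aim 3 and inform the planning of later trials. A statement that MMG is comparable to PCGT on PTSD, depression and suicidality could enter that discussion when the data are also compatible with MMG being materially worse.

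**Working it through.** **Inputs from the article**
- Allocation per cycle: "the MMG (n=8) or PCGT control (n=8). The process will be repeated for the second cohort". Two cycles of 8 + 8 give 2 × 16 = 32, or 16 per arm. This reproduces the stated total. No power calculation accompanies it, so there is no power figure to reproduce.
- About 7 enrolled men are expected to drop out of treatment (Aim 3, Data Collection). 32 − 7 = 25, about 12.5 per arm.

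**Assumptions, because the article gives no figures**
- Two-sided alpha of 5%, results in SD units, and no clustering unless stated.
- Baseline correlation r of 0 (unadjusted), 0.5 or 0.7.
- Deficits and margins of 0.3 to 0.8 SD, for illustration.

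**Step 1. Interval half-width**

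Half-width = t(0.975, df) × √(2v/n), where v is the variance factor: 1 unadjusted, 1 − r² with baseline as a covariate, 2(1 − r) for a change score.
- Unadjusted, n = 16: 2.042 × √(2/16) = 2.042 × 0.354 = 0.72 SD.
- Covariate, r = 0.7: v = 0.51, and 2.045 × √(2 × 0.51/16) = 2.045 × 0.252 = 0.52 SD.
- Change score, r = 0.7: v = 0.60, and 2.042 × √(2 × 0.60/16) = 2.042 × 0.274 = 0.56 SD.
- Change score, r = 0.5: v = 1, so 0.72 SD again.

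**Step 2. Chance that a true deficit is non-significant**

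Noncentral t with noncentrality d/√(2v/n), 16 per arm:

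| Analysis | 0.5 SD deficit | 0.8 SD deficit |
|---|---|---|
| Unadjusted | 72% | 41% |
| Covariate, r = 0.5 | 65% | 29% |
| Change score, r = 0.7 | 58% | 19% |
| Covariate, r = 0.7 | 52% | 13% |

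If all 7 dropouts also lacked outcome data (12.5 per arm), the unadjusted figures would be 78% and 52%, with a half-width of 0.83 SD. The article does not say that men who leave treatment skip the surveys, so this is a pessimistic case.

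**Step 3. Could a margin rescue the claim at this size?**

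Chance of showing non-inferiority at an assumed 0.5 SD margin (one-sided 2.5%, true difference 0, 16 per arm): 28% unadjusted, 42% for a change score with r = 0.7, 48% with baseline as a covariate and r = 0.7.

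Number per arm for 80% power, unadjusted: 2 × (1.96 + 0.84)²/margin².
- Margin 0.3 SD: 175 per arm.
- Margin 0.5 SD: 63 per arm.
- Margin 0.8 SD: 25 per arm.

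With 16 per arm, the smallest margin with 80% power is (1.96 + 0.84) × √(2/16) ≈ 0.99 SD.

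**Step 4. Clustering by therapy group**

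With groups of 8 and an assumed intraclass correlation of 0.05 to 0.10, the design effect is 1 + 7 × 0.05 = 1.35 to 1 + 7 × 0.10 = 1.70. An interval that allowed for it would have a half-width of 1.96 × √(1.35 × 2/16) = 0.81 to 1.96 × √(1.70 × 2/16) = 0.90 SD (normal approximation). The model as described lists only group and time. If clustering exists but is not modelled, the test rejects more often: in simulation, a 0.5 SD deficit is non-significant about 68 to 69% of the time at 0.05 and 66% at 0.10, against 72% without clustering.

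**The case against.** The strongest reply is that this is an exploratory pilot that says so. Every scale is labelled exploratory, low power is stated in the Analysis section and again among the limitations, and main treatment effects are left to later trials. That lowers the severity. But those statements disclaim efficacy. They do not bar a claim of comparability, which low power makes easier to reach.

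A second reply is that a reader might infer that the investigators will report non-significance as comparability. The article does not say that. It gives no alpha, p-value rule or decision rule, and a mixed model gives estimates and intervals as readily as tests. The supportable statement is that a null result *could* be read this way.

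Third, a reader might infer that such a reading would trigger the multisite trial. The documents do not support this: the Discussion makes that step depend on feasibility and a viable implementation pathway.

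Fourth, a margin may sit in an analysis plan that is not shown, so its absence from a condensed article is not itself the fault. The mismatch between hypothesis and analysis remains, and step 3 shows that a margin of 0.3 to 0.5 SD would have little chance of being met with 32 men.

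Fifth, the figures depend on the assumed correlation, margin and alpha. This is correct, and they are given as ranges for that reason.

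**Conclusion.** The point stands as a moderate one. The article pairs a comparability hypothesis on all five scales with a between-group comparison that it calls underpowered, and it gives comparable no testable meaning. Under two-sided 5% alpha, 16 per arm and no clustering, the interval half-width is about 0.72 SD unadjusted and about 0.5 to 0.6 SD at a baseline correlation of 0.7. A true 0.5 SD deficit would be non-significant about 52 to 72% of the time, and non-inferiority at an assumed 0.5 SD margin would be shown about 28 to 48% of the time with truly equal arms.

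Two stronger readings should be avoided. The hypothesis is not unfalsifiable: an unadjusted test with 16 per arm would detect a 1.0 SD deficit about 78% of the time. Nor does clustering worsen every figure: it widens an interval that allows for it, but slightly lowers the non-significance rate of a test that ignores it.

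**What to change.** In the aim 2 Analysis section:

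1. Drop the comparability hypothesis for RAS, EISS, GBS, PCL-5, PHQ-9 and suicidality. The attendance hypothesis is not affected by this point.
2. Say that the MMG minus PCGT difference from the mixed model will be reported with 95% confidence intervals at posttreatment and at 6 months, as exploratory estimates. Removing p-values is optional.
3. Add one sentence that a non-significant difference will not be interpreted as comparability, and that any such claim is left to the later fully powered trial with a margin stated in advance.

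No larger sample is needed. The article reports that aim 2 recruitment has not begun, so the change can be made before any trial data exist. The cost is a few sentences of text and giving up a claim that the pilot cannot support.
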